**Other:**

- Assessment of the PK of ceftobiprole in subjects treated with ceftobiprole
- Collection of MRU data that may be used in future economic modeling

**Safety/Tolerability**

- Safety and tolerability of treatment with ceftobiprole in subjects hospitalized with CAP.

**11.3.3. Subject Baseline Characteristics and Disposition**

Demographics and baseline characteristics will be summarized descriptively.

Subject disposition will be summarized, including the numbers of subjects who prematurely discontinued the trial treatment, who underwent the TOC visit and who returned for the LFU visit.

Subjects who discontinued treatment prematurely will be listed and summarized, including details of the reasons for discontinuation.

Concomitant treatments will be summarized descriptively.

**11.3.4. Analysis of Primary Parameter**

The primary analysis of clinical cure rate will be based on the CE population and the ITT population as coprimary populations.

A noninferiority hypothesis will be assessed based on clinical cure rates at the TOC visit. The hypotheses will be:

- $H_0$ : The clinical cure rate of ceftobiprole is more than 10% inferior to that of the comparator.
- $H_1$ : The clinical cure rate of ceftobiprole is not more than 10% inferior to that of comparator.

This hypothesis will be operationally tested by presenting the 2-sided 95% confidence limits of the between treatment difference in clinical cure rate at the TOC visit. In order to claim noninferiority, the lower bound of the 2-sided 95% confidence interval must be  $\geq -10\%$ .

In addition, clinical outcome at the TOC visit will be summarized descriptively by initial pathogen, subject subgroups defined by age (<65 versus ≥65 years), by sex (men versus women), and by race.

The analysis of clinical cure rate will be performed in the mITT populations as well. Subjects in the ITT and mITT populations whose clinical outcome is assessed as missing or Not Evaluable, will be included in the analysis of clinical outcome as failures.

Exploratory analyses of clinical outcome (cure versus failure) based on logistic regression models adjusting for geographical region and baseline factors may be performed.

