## 5.2. Procedures

Subjects will be assigned to 1 of 2 treatment groups based on a computer-generated randomization schedule prepared by the sponsor before the study. The randomization will be balanced between the 2 treatment groups by using randomly permuted blocks. Subjects will be stratified at entry by PSI score to 1 of 2 strata:  $\leq 90$  and  $\geq 91$ . Subjects will also be stratified by the need for anti-staphylococcal therapy (placebo or linezolid) based on signs, symptoms, and medical history at enrollment. Based on this randomization code, the study drug will be packaged and labeled for each subject. Medication code numbers will be preprinted on the study drug labels and assigned as subjects qualify for the study and are randomly assigned to treatment. An unblinded monitor will perform drug accountability.

Central randomization will be implemented in conducting this study. The subject number and treatment regimen will be assigned after phoning into the Interactive Voice Response System (IVRS) provided by a vendor designated by the sponsor. The caller must use their own user ID and PIN, and then give the requested subject details (e.g., subject initials and subject's date of birth). Based on this information, the IVRS will assign a unique subject number and treatment regimen, which will dictate the treatment assignment for that subject.

The investigator will not be provided with randomization codes. The codes will be maintained within the IVRS, which has the functionality to allow the investigator to break the blind for an individual subject.

Under normal circumstances, the blind should not be broken until all subjects have completed the study and the database is finalized. Otherwise, the blind should be broken only if specific emergency treatment would be dictated by knowing the treatment status of the subject. In such cases, the investigator must contact the sponsor. If the investigator is unable to contact the sponsor, the investigator may in an emergency determine the identity of the treatment by telephoning IVRS. The sponsor must be informed as soon as possible. The date, time, and reason for the unblinding must be documented in the appropriate section of the case report form (CRF) and in

the source document. The fax copy received from the IVRS indicating the code break must be retained with the CRF.

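### Randomization is stratified by PSI and anti-staphylococcal need, but the primary confidence interval is not stated to account for either factor and neither is a listed subgroup; the precision at stake is small

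*Protocol*

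**What the plan says.** **Randomization.** Section 5.2 (and likewise 3.1) names two stratification factors. On the first: "Subjects will be stratified at entry by PSI score to 1 of 2 strata", split at 90/91. On the second: "Subjects will also be stratified by the need for anti-staphylococcal therapy (placebo or linezolid) based on signs, symptoms, and medical history at enrollment".

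**Primary analysis.** Sections 9.4 and 11.3.2 define the clinical cure rate as cured subjects divided by everyone in the population at TOC. Section 11.3.4 says the noninferiority hypothesis is to be "operationally tested by presenting the 2-sided 95% confidence limits of the between treatment difference in clinical cure rate at the TOC visit". The decision rule begins "In order to claim noninferiority, the lower bound of the 2-sided 95% confidence interval must be" and sets the limit at −10%. The analysis is "based on the CE population and the ITT population as coprimary populations". No interval method is named.

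**Adjustment.** Section 11.3.4 mentions exploratory analyses of cure versus failure "based on logistic regression models adjusting for geographical region and baseline factors may be performed". The baseline factors are not identified.

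**Subgroups.** Clinical outcome at TOC is to be "summarized descriptively by initial pathogen, subject subgroups defined by age", and also by sex and race. Neither PSI stratum nor anti-staphylococcal need is in the list.

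**The concern.** The design balances the arms on two factors that the protocol treats as markers of severity. Section 1.2 says PSI quantifies short-term mortality risk, and that pneumonia due to *S. aureus* tends to be more severe. The stated primary analysis then makes no use of either. Read as written, a difference of two whole-population ratios is an unstratified estimate.

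After stratified allocation, the usual unstratified variance still includes between-stratum variation that the allocation has removed from the treatment comparison. The interval then errs on the wide side. Any loss matters most in ITT, where subjects with a missing or not evaluable outcome count as failures and the variance is larger.

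A separate matter is description. The objective is noninferiority to ceftriaxone with or without linezolid, but no outcome summary is planned by severity stratum or by the baseline marker of the intended comparator form.

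**Working it through.** **The plan's own figures.** The protocol gives no interval width, so the only figure to reproduce is the sample size in Section 11.1.
- From 90% cure in both arms, a 10-point margin, two-sided 5% and 80% power: n = (1.960 + 0.842)² × 2 × 0.90 × 0.10 / 0.10² ≈ 142 per arm, not 266.
- 266 per arm gives about 97% power.
- The inflation does reproduce: 532 / 0.80 = 665, close to 670.

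The mismatch is a separate point. Here it only shows that CE has power to spare, so ITT is where a narrower interval could help.

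**Inputs from the protocol.** 266 CE subjects per arm; 670/2 = 335 ITT subjects per arm; 90% cure in CE.

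**Assumptions (not in the protocol).** ITT cure 0.80 × 0.90 = 72%, with all nonevaluable subjects counted as failures. Share with PSI ≥91 of 20 to 50%. Cure-rate gap between PSI strata of 5 to 20 points. No true treatment difference, and arms balanced within strata.

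**Formulas.** Let p be the overall cure rate, w the share with PSI ≥91 and g the gap.
- Unstratified variance per subject: V0 = p(1 − p).
- Stratified variance: V1 = sum of (stratum share × stratum p(1 − p)) = V0 − w(1 − w)g².
- Half-width = 1.96 × √(2V/n).
- Power = Φ(0.10/√(2V/n) − 1.96).

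**Results.**

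| Population | w | g | V | Half-width (points) | Narrower by | Power |
|---|---|---|---|---|---|---|
| CE, unstratified | – | – | 0.0900 | 5.099 | – | 0.9702 |
| CE | 0.20 | 0.05 | 0.0896 | 5.087 | 0.22% | 0.9708 |
| CE | 0.40 | 0.10 | 0.0876 | 5.030 | 1.34% | 0.9736 |
| CE | 0.40 | 0.20 | 0.0804 | 4.819 | 5.48% | 0.9825 |
| ITT, unstratified | – | – | 0.2016 | 6.800 | – | 0.8219 |
| ITT | 0.20 | 0.05 | 0.2012 | 6.793 | 0.10% | 0.8226 |
| ITT | 0.40 | 0.10 | 0.1992 | 6.759 | 0.60% | 0.8263 |
| ITT | 0.50 | 0.20 | 0.1916 | 6.629 | 2.51% | 0.8406 |

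The first and last stratified rows for each population are the extremes of the grid. In CE, w = 0.50 with g = 0.20 is left out because it would need 100% cure in the low-PSI stratum. The largest reductions are 5.099 − 4.819 = 0.28 points in CE and 6.800 − 6.629 = 0.17 points in ITT.

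**Both factors (four strata).** With 40% at PSI ≥91, 10% needing anti-staphylococcal therapy, PSI gaps of 5 to 15 points and anti-staphylococcal gaps of 10 to 20 points, the half-width falls by 0.8 to 5.1% in CE (to 5.056–4.837) and by 0.4 to 2.3% in ITT (to 6.774–6.646).

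**Validity.** In simulation (40,000 runs, balanced strata) at a true difference of −10 points, the unstratified interval claimed noninferiority 2.3 to 2.5% of the time and the stratified interval about 2.6%. Monte Carlo error is about √(0.025 × 0.975/40,000) = 0.08 points (one standard error). The unstratified interval is therefore valid to slightly conservative.

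**The case against.** The strongest reply is that Section 11.3.4 does not choose a crude interval. It names no method and never says unadjusted. A Mantel-Haenszel or stratified Miettinen-Nurminen interval would satisfy the sentence, and the SAP, which Section 11.4 refers to but which is not at hand, may specify one. This stands: a reader might infer that the protocol has fixed a crude analysis, and the text does not support that. What remains is that the plain reading is unstratified, since the cure rate is a whole-population ratio and the only adjustment mentioned is optional and exploratory.

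Other inferences also go too far:
- **That the missing subgroups widen the interval.** They do not. Descriptive summaries have no bearing on interval width, so the two matters are separate.
- **That stratifying would save some tens of the 670 subjects.** Section 1.2 ties PSI to mortality, not to cure at TOC, and no cure rate by stratum is given. With small gaps the gain is close to nil, and a reduction computed in CE applies to 532 subjects, not 670.
- **That the trial cannot examine each comparator form.** Both factors are recorded at entry, and outcome by initial pathogen is already planned. The anti-staphylococcal stratum does not identify treatment received either: under Section 6.1.3 linezolid/placebo may be added or stopped after randomization according to culture, Gram stain and sensitivity results. A subgroup by stratum would answer that question only in part.

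It is also fair to say that the change needs a weighting choice and a pooling rule, which are details often settled in an SAP.

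**Conclusion.** The point holds as a modest gain in precision. The protocol randomizes by two factors and, as written, brings neither into the primary analysis or the subgroup list. If the interval is computed without them, the claim of noninferiority is still sound, because the interval is valid to slightly conservative.

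Set against a 10-point margin, the possible narrowing is small in both populations. Power at no true difference rises by at most about 1.2 points in CE (0.9702 to 0.9825) and 1.9 points in ITT (0.8219 to 0.8406). These sizes rest on assumed stratum shares and gaps and, for ITT, on the assumed 72% cure rate. They would be larger only if the strata differed by more than 20 points. The reason to act is that the change costs almost nothing and settles the estimator before unblinding.

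**What to change.** In Section 11.3.4, state that the primary 95% CI for the difference in cure rate, in both CE and ITT, is stratified by PSI (≤90, ≥91) and need for anti-staphylococcal therapy, using Mantel-Haenszel weights or the stratified Miettinen-Nurminen method. Use the strata as recorded in the IVRS at randomization, not later linezolid use, which is a post-randomization event. Prespecify that the anti-staphylococcal factor is pooled if a cell is sparse, with the threshold stated. Keep the unstratified CI as a sensitivity analysis. If the SAP already specifies a stratified interval, a matching sentence here is enough.

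Separately, add both factors to the descriptive subgroups for clinical outcome at TOC, with a note that the anti-staphylococcal stratum is only a baseline marker of the intended comparator form.

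The cost is a choice of weights, a pooling rule and a few tables. Randomization, sample size and conduct are unaffected.

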#### **11.3.5. Analysis of Secondary Parameters**

Microbiological eradication rate will be analyzed in a similar manner to clinical cure rate at the TOC visit. In addition, microbiological eradication rate at the TOC visit will be summarized descriptively by infection type and initial pathogen as well as by subjects with and without quantitative respiratory culture at baseline.

The status of subjects with clinical cure at the TOC visit with regard to relapse (failure at the LFU visit) will be summarized descriptively.

The correlation between cure and microbiological eradication rates will be presented descriptively in the form of frequency tables.

The 30-day pneumonia-specific mortality rate will be analyzed to compare the 2 treatment groups using a Fisher's exact test.

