## 2. OBJECTIVES

The primary objective is to demonstrate the noninferiority of ceftobiprole medocaril compared with ceftriaxone with/without linezolid (comparator) with respect to the clinical cure rate in subjects hospitalized with CAP at the TOC visit.

The secondary objectives are:

- To compare the microbiological eradication rate following treatment with ceftobiprole versus the comparator in subjects with hospitalized CAP at the TOC visit
- To compare the clinical cure rate following treatment with ceftobiprole versus the comparator of hospitalized CAP subjects that require mechanical ventilation within the first 48 hours of enrollment
- To compare the microbiological eradication rate following treatment with ceftobiprole versus the comparator of hospitalized CAP subjects that require mechanical ventilation within the first 48 hours of enrollment
- To compare the clinical and microbiological relapse rates following treatment with ceftobiprole versus the comparator in subjects with hospitalized CAP at the late follow-up (LFU) visit

To compare the 30-day pneumonia-specific mortality rates following treatment with ceftobiprole or the comparator of hospitalized CAP subjects

Other objectives are:

- To assess the PKs of ceftobiprole in subjects treated with ceftobiprole
- To collect medical resource utilization (MRU) data that may be used in future economic modeling

Safety/tolerability objectives are:

- To characterize the safety and tolerability of treatment with ceftobiprole in subjects hospitalized with CAP

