At the LFU assessment, the TOC clinical outcome of failure or unable to evaluate will be carried forward as the LFU outcome assessment. Subjects with TOC clinical outcome of cure will be categorized at the LFU assessment as:

***Cure:*** no further antimicrobial therapy was necessary for treatment of the infection.

***Relapse:*** signs and symptoms of CAP reappeared such that additional antimicrobial therapy was necessary. Relapse will be categorized as failure at LFU.

***Unable to evaluate:*** Absence of clinical assessments at LFU, or concomitant treatment with a systemic antibiotic active against gram-positive or gram-negative respiratory bacteria, administered for a reason other than the CAP.

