## 11. STATISTICAL METHODS\*

### 11.1. Sample Size Determination

The sample size determination is based on a noninferiority test of ceftobiprole versus the comparator in terms of the primary efficacy parameter, clinical cure rate. The assumptions on which the sample size estimate is based are as follows:

- Clinical cure rates of 90% for both randomized study treatments ceftobiprole and the comparator
- Limit of noninferiority of ceftobiprole versus the comparator is 10%
- Type 1 error probability ( $\alpha$ ) = 0.05 (2 sided)
- Type 2 error probability ( $\beta$ ) = 0.2 (power = 0.8 = 1 –  $\beta$ )
- The evaluable rate is 80%.

Based on these assumptions, 670 subjects will need to be randomized to ensure 532 clinically evaluable subjects, 266 subjects in each treatment group.

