### **11.3.2. Definition of Parameters**

#### **Primary**

- Clinical cure rate, defined as the ratio of the number of clinically cured subjects to the total number of subjects in the population, at TOC visit.

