#### **Secondary**

- Microbiological eradication rate, defined as the ratio of the number of subjects with microbiological eradication or presumed eradication to the total number of subjects in the population at TOC visit.
- Clinical cure rate following treatment with ceftobiprole versus the comparator of hospitalized CAP subjects that require mechanical ventilation within the first 48 hours of enrollment

---

\* This section of the protocol has been revised. Please refer to the section of this document entitled PROTOCOL AMENDMENTS (Amendment INT-3, 22 December 2006) for a detailed description of the specific changes.

- Microbiological eradication rate following treatment with ceftobiprole versus the comparator of hospitalized CAP subjects that require mechanical ventilation within the first 48 hours of enrollment.
- Clinical and microbiological relapse at LFU visit
- Thirty-day pneumonia-specific mortality rates following treatment with ceftobiprole or the comparator.

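### Clinical relapse is a between-arm objective, but its only planned analysis is a descriptive table among test-of-cure cures, which is not a randomized comparison

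*Protocol*

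**What the plan says.** Protocol Section 2 and the Synopsis list, among the secondary objectives, a comparison of clinical and microbiological "relapse rates following treatment with ceftobiprole versus the comparator in subjects with hospitalized CAP at the late follow-up (LFU) visit". No subset is named in that objective, whereas the two objectives on ventilated subjects in the same list do name theirs.

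Section 11.3.2 lists the parameter as "Clinical and microbiological relapse at LFU visit" and gives neither numerator nor denominator. By contrast, the primary parameter is defined there as "the ratio of the number of clinically cured subjects to the total number of subjects in the population, at TOC visit".

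Section 9.3.1 sets the LFU categories. Relapse is open to TOC cures only: "Subjects with TOC clinical outcome of cure will be categorized at the LFU assessment as" cure, relapse or unable to evaluate. For everyone else, "the TOC clinical outcome of failure or unable to evaluate will be carried forward as the LFU outcome assessment". It adds: "Relapse will be categorized as failure at LFU".

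Section 11.3.5 then gives the analysis of clinical relapse: "The status of subjects with clinical cure at the TOC visit with regard to relapse (failure at the LFU visit) will be summarized descriptively". In the same section, eradication is to be handled in the way clinical cure is, and 30-day pneumonia mortality is compared with Fisher's exact test. Nothing in Sections 11.3.4 to 11.3.6 analyses LFU cure or failure over a whole analysis population.

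**The concern.** The objective asks how the arms compare on durability of response. The only table serving it starts from subjects already cured at TOC. That condition is met after randomization and is the very outcome the treatments are meant to affect. Subjects who would have been marginal cures on one arm may be failures at TOC on the other. They then leave the relapse table altogether, and the subjects who remain are a more robust group.

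The direction is awkward for a noninferiority trial. A treatment that fails more subjects by TOC has fewer fragile cures left to relapse. It can show the lower relapse rate even though no more of its subjects are well at LFU. A reader who takes the relapse table as the answer to the secondary objective could credit that arm with better durability. The point concerns clinical relapse; the sentence in Section 11.3.5 does not deal with microbiological relapse.

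**Working it through.** **Plan's own figure.** The protocol states no expected relapse rate, so there is none to reproduce. Two planning figures are used: "Clinical cure rates of 90% for both randomized study treatments ceftobiprole and the comparator" and 266 clinically evaluable subjects per arm, both from Section 11.1.

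**Definitions.** Let *c* be the proportion cured at TOC and *s* the proportion cured at TOC and still cured at LFU, both over all subjects in the arm.

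- Relapse among TOC cures (the Section 11.3.5 table): (c − s)/c = 1 − s/c
- Relapse over all subjects: c − s
- Cure at LFU with TOC failures carried forward: s

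For fixed *s*, the first two quantities both fall as *c* falls. Only the third does not depend on *c*. This is an identity and needs no data.

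**Illustration.** 266 per arm with complete LFU data. Arm A has the planned 90% TOC cure. Arm B's 85% and the relapse counts are assumptions.

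| | Arm A | Arm B |
|---|---|---|
| TOC cures | 239 | 226 |
| TOC failures | 27 | 40 |
| Relapses by LFU | 24 | 11 |
| Cured at LFU | 215 | 215 |
| Relapse among TOC cures | 24/239 = 10.0% | 11/226 = 4.9% |
| Relapse over all subjects | 24/266 = 9.0% | 11/266 = 4.1% |
| Cure at LFU over all subjects | 215/266 = 80.8% | 215/266 = 80.8% |

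The gap in relapse among TOC cures is 5.2 points, with standard error √(0.1004 × 0.8996/239 + 0.0487 × 0.9513/226) = 0.0241. The Wald 95% interval is 0.4 to 9.9 points, in favour of the arm with 13 more TOC failures. The difference in cure at LFU is 0.

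**Denominator alone.** The third row from the end and the one below it show that replacing TOC cures by all subjects changes little: the gap is still 9.0 − 4.1 = 4.9 points. It vanishes only when TOC failures also count as LFU failures.

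**Range.** Keep arm A at 90% TOC cure, let arm B's TOC cure run from 82% to 85%, and set sustained cure at 80% or 81% in both arms. The gap among TOC cures is then about 5.2 to 8.8 points. For example, at 80% sustained cure and 85% TOC cure it is (1 − 0.80/0.90) − (1 − 0.80/0.85) = 11.1% − 5.9% = 5.2 points. At 81% and 82% it is 10.0% − 1.2% = 8.8 points.

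**Could it sit beside a successful primary result?** Take TOC cure of 86% versus 90% and sustained cure of 82% in both arms. The TOC difference is −4 points, with standard error √((0.86 × 0.14 + 0.90 × 0.10)/266) = 0.0281. The Wald lower bound is −4 − 1.96 × 2.81 = −9.5 points, which meets the −10% criterion of Section 11.3.4. Relapse among cures is 1 − 0.82/0.86 = 4.7% versus 1 − 0.82/0.90 = 8.9%. Noninferiority could therefore be claimed on a numerically lower cure rate while the same arm shows about half the relapse.

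**The case against.** The strongest reply is that relapse presupposes cure. A subject never cured cannot relapse, and Section 9.3.1 reserves the category for TOC cures, so Section 11.3.5 simply applies the protocol's own definition. This stands. A reader might infer a flat contradiction, with the objective covering all hospitalized subjects and the analysis covering only some. The objective names the disease population and does not say all, so the documents do not support that reading.

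A reader might also infer that Section 11.3.5 equates relapse with a different, wider LFU failure. It does not. The words apply to TOC cures, and within that group relapse and LFU failure are the same thing.

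Nor do the documents support reading the table as a route to a false claim. It carries no test and no confidence interval. A TOC deficit would appear in the coprimary CE and ITT analyses. Pneumonia deaths beyond the first 48 hours count as TOC failures, and 30-day pneumonia mortality is compared separately. The interval of 0.4 to 9.9 points measures the size of an illustration, not an analysis the protocol plans.

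Finally, the statistical analysis plan is not shown and could add an LFU cure table. However, the point rests on what the protocol fixes: the restricted set and the descriptive method for an objective worded as a comparison. The other two analyses in the same section are comparative. What survives is that no planned clinical analysis answers the durability objective on a randomized footing.

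**Conclusion.** The point holds as a limited one. The relapse table in Section 11.3.5 is valid as a description of what happens after cure, but it is not a randomized between-arm comparison and should not stand alone for an objective that calls for one. At equal sustained cure, it favours the arm with more TOC failures. That direction follows from 1 − s/c and does not depend on assumed rates.

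The size does depend on them. The illustration gives 10.0% versus 4.9% at equal sustained cure of 80.8%, and the range examined gives 5.2 to 8.8 points. These figures rest on an assumed TOC gap (5 points in the main illustration), assumed sustained cure and complete LFU data; only the 90% and the 266 per arm come from the protocol. The primary conclusion is untouched. This is a cheap improvement to one secondary endpoint.

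**What to change.** In Sections 11.3.2 and 11.3.5, add clinical cure at LFU: cured at TOC and not relapsed, with TOC failures carried forward as Section 9.3.1 already provides. Take it over all subjects in the ITT and CE populations. Report the 2-sided 95% confidence interval of the between-arm difference, and name this as the comparison that serves the objective.

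State how incomplete LFU outcomes count:

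- **ITT:** count missing or unable-to-evaluate LFU outcomes as failures, as Section 11.3.4 does for TOC.
- **CE:** write down the rule for TOC cures who are unable to evaluate at LFU, since the protocol gives none for this analysis.

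Keep the relapse table as a descriptive summary, labelled as conditional on TOC cure. Changing only its denominator would not help.

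The cost is one extra secondary analysis and a few lines of text. No new data are needed, because the LFU categories are already collected or carried forward.

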## 1.2. Overall Rationale for the Study

Despite the availability of effective antimicrobial agents, CAP remains a potentially life-threatening disease. Although most patients with CAP are treated as outpatients, approximately 20% of patients with CAP are hospitalized (18% on medical wards and 2% in intensive care units [ICUs]). The Pneumonia Outcomes Research Trial (PORT) developed a clinical prediction rule that quantifies short-term mortality risk for subjects with CAP. The PORT Severity Index (PSI) was validated in 2 independent samples and had a high ability to discriminate between those patients who were at a high risk of dying and those who were not. Thus, the PSI will be used to stratify subjects based on initial pneumonia severity.

The overall mortality rate among patients requiring hospitalization for CAP ranges from 5% to 25% and rises to 20% to 50% in those with severe CAP requiring treatment in the ICU. Bacteremia is a potential complication in patients with CAP, especially those who are hospitalized, and raises the mortality rate approximately 3-fold. Thus, it is especially important to treat CAP patients who require hospitalization with an antimicrobial agent that achieves effective concentrations in plasma and pulmonary tissues and is bactericidal against the most common etiologic agents. *Streptococcus pneumoniae* is the most common etiologic agent isolated from hospitalized

patients with CAP, especially those with severe disease. Other less common causative agents include *S. aureus*, *L. pneumophila*, *H. influenzae* and the enteric gram-negative bacilli. Although *S. aureus* is not a common cause of CAP in otherwise healthy patients, this pathogen can be an important cause of pneumonia in patients with diabetes, patients who abuse i.v. drugs, patients with renal failure, and patients who develop secondary bacterial infections during influenza epidemics. Pneumonia due to *S. aureus* tends to be a more severe infection and frequently requires hospitalization.

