## Hypotheses

### Efficacy:

The clinical cure rate, with respect to treatment with ceftobiprole with/without switch to oral therapy, will be noninferior to a regimen of the comparator, with/without a switch to oral therapy, in the clinically evaluable subjects hospitalized with CAP.

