### Safety and tolerability:

The safety and tolerability of treatment with ceftobiprole will be similar to a regimen of the comparator in hospitalized CAP subjects.

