### **Secondary Endpoints**

- Microbiological eradication rate at TOC visit
- Clinical cure rate in subjects requiring mechanical ventilation within 48 hours of enrollment
- Microbiological cure rate in subjects requiring mechanical ventilation within 48 hours of enrollment

---

\* This section of the protocol has been revised. Please refer to the section of this document entitled PROTOCOL AMENDMENTS (Amendment INT-3, 22 December 2006) for a detailed description of the specific changes.

- Clinical and microbiological relapse at LFU visit
- Thirty-day pneumonia-specific mortality rates (all deaths due to pneumonia within 30 days after randomization).

For the definition of these parameters see Section 11.4.2, Definition of Parameters.

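### 30-day pneumonia mortality is compared only by a Fisher's exact test of equality, which cannot show how large an excess of deaths the trial excludes

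*Protocol*

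**What the plan says.** The mortality objective in Section 2 is "To compare the 30-day pneumonia-specific mortality rates following treatment with ceftobiprole or the comparator of hospitalized CAP subjects". Section 9.4 lists it as a secondary endpoint, counting pneumonia deaths up to 30 days from randomization. Section 11.3.5 gives the analysis in one sentence: "The 30-day pneumonia-specific mortality rate will be analyzed to compare the 2 treatment groups using a Fisher's exact test". It names no interval, significance level or analysis population.

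The neighbouring efficacy endpoints are treated differently. For the primary endpoint, Section 11.3.4 says "This hypothesis will be operationally tested by presenting the 2-sided 95% confidence limits of the between treatment difference in clinical cure rate at the TOC", with the lower limit held against a 10-point margin. Section 11.3.5 then has microbiological eradication analyzed in the same way as cure, which on a natural reading brings the same confidence limits.

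The efficacy hypothesis is "The clinical cure rate, with respect to treatment with ceftobiprole with/without switch to oral therapy, will be noninferior to a regimen of the comparator". The safety hypothesis is "The safety and tolerability of treatment with ceftobiprole will be similar to a regimen of the comparator in hospitalized CAP subjects". Neither mentions mortality by name.

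On size, Section 11.1 says "670 subjects will need to be randomized to ensure 532 clinically evaluable subjects, 266 subjects in each treatment group". Those numbers were set for the cure rate. No rate, power or detectable difference is given for mortality. The nearest figure is in Section 1.2, which puts overall mortality in hospitalized CAP at 5% to 25%.

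**The concern.** Fisher's exact test takes equal mortality as its null hypothesis. Rejection would be informative, but in a trial of this size and purpose the likelier result is non-rejection, and the p-value then says nothing about how many extra deaths remain compatible with the data. A confidence interval does. Within one section, a microbiological endpoint gets an interval and death does not.

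The stake is interpretation. If the cure rate meets its margin and the mortality test is non-significant, the two results will be reported together, and a reader could take the second as evidence that mortality is not increased. If pneumonia deaths are few, that inference would have little behind it.

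**Working it through.** **Inputs.** There is no stated mortality power to reproduce, so only the arm size is taken from the plan.

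- Randomized: 670 at 1:1 (Sections 3.1 and 11.1), so 670 / 2 = 335 per arm. The evaluability step is consistent: 532 / 0.80 = 665, close to 670.
- Clinically evaluable: 266 per arm (Section 11.1), used as a sensitivity case.
- Test: two-sided Fisher's exact at 5%. The level is an assumption, carried over from the primary analysis.
- Comparator pneumonia mortality: not given. A range is shown. Rates below 5% are assumptions; 5% is the low end of the overall-mortality range in Section 1.2.

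**Chance of missing a true doubling.** With comparator risk p and ceftobiprole risk 2p,

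miss = 1 − Σₓ Σᵧ Bin(x; n, p) · Bin(y; n, 2p) · I[Fisher p-value(x, y) ≤ 0.05],

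summed over all possible pairs of death counts.

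| True risks | Miss, n = 335 per arm | Miss, n = 266 per arm |
|---|---|---|
| 1% vs 2% | 89.5% | 92.5% |
| 2% vs 4% | 74.0% | 80.7% |
| 3% vs 6% | 60.0% | 68.2% |
| 4% vs 8% | 47.2% | 56.6% |
| 5% vs 10% | 35.6% | 45.7% |
| 8% vs 16% | 12.4% | 21.7% |
| 10% vs 20% | 5.4% | 11.8% |

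**Smallest significant split at 335 per arm.** With 5 comparator deaths, p ≤ 0.05 needs 15 ceftobiprole deaths (15 / 5 = 3.0-fold). With 10, it needs 22 (22 / 10 = 2.2-fold).

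**What an interval adds.** Take 14 ceftobiprole and 7 comparator deaths.

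- Risks: 14 / 335 = 4.18% and 7 / 335 = 2.09%. Difference: +2.09 points.
- Fisher p = 0.18.
- Wilson 95% limits: 2.51% to 6.89% (ceftobiprole) and 1.02% to 4.25% (comparator).
- Newcombe lower limit: 2.09 − √[(4.18 − 2.51)² + (4.25 − 2.09)²] = 2.09 − 2.73 = −0.6 points.
- Newcombe upper limit: 2.09 + √[(6.89 − 4.18)² + (2.09 − 1.02)²] = 2.09 + 2.91 = +5.0 points.

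The Miettinen-Nurminen score interval gives the same limits to one decimal. With 10 versus 5 deaths, p = 0.30 and the Newcombe interval is −0.9 to +4.1 points. In both cases the p-value reports only non-significance, while the interval shows that an excess of 4 to 5 points has not been excluded.

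**Does the primary endpoint already cover this?** Only in part.

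- The failure definition in Section 9.3.1 counts pneumonia deaths only when they occur more than 48 hours after the first infusion.
- The primary is read at test-of-cure, 7 to 14 days after the last dose. With 5 to 7 days of treatment that is about Day 5 + 7 = 12 to Day 7 + 14 = 21, so later deaths up to Day 30 fall outside it.
- Its margin is 10 points on all failures, so a mortality excess of several points could fit inside it.

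**The case against.** The strongest reply has four parts.

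First, the objective only calls for a comparison, and Fisher's exact test is a legitimate way to compare two small proportions. That stands: the test is valid. The point is that it should not be the main analysis on its own.

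Second, a reader might infer that the protocol intends p>0.05 to count as evidence of similarity. The documents do not support that. No section states such a rule, noninferiority is attached to the cure rate, and the similarity hypothesis concerns safety and tolerability, whereas 30-day mortality is listed among the efficacy endpoints. The misreading is a risk and not a stated plan. For the same reason, this sentence gives no ground for rewording the safety hypothesis.

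Third, an accompanying interval may be in the statistical analysis plan, which is not shown. This limits the finding but does not remove it. The protocol does name a method here, chosen in Amendment INT-3 as a correction, and what is at issue is that choice of main analysis.

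Fourth, mortality is protected elsewhere. Later pneumonia deaths are failures in the primary endpoint, missing or non-evaluable outcomes count as failures in the intent-to-treat analysis, and the data monitoring committee sees unblinded safety and efficacy data. This is true, but a composite cure rate at test-of-cure and trial monitoring do not estimate the 30-day mortality difference.

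**Conclusion.** The point holds in a limited form. The protocol fixes an equality test as the only named between-arm analysis of 30-day pneumonia mortality, and that test cannot bound an excess of deaths, whatever the underlying rate.

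The size depends on an unknown rate. With 335 per arm, all randomized subjects analyzed and a two-sided 5% level, a doubling is missed 90% to 36% of the time for comparator rates of 1% to 5%. Those rates are assumptions. It would be wrong to read low power across the whole 5% to 25% overall-mortality range: a doubling from 8% is missed 12% of the time, and from 10% only 5%.

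This concerns a secondary endpoint and does not affect the primary conclusion. It should be changed because the better analysis is simple and uses the same data.

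**What to change.** In Section 11.3.5:

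- Make the main analysis of 30-day pneumonia-specific mortality the between-arm risk difference, ceftobiprole minus comparator, with a two-sided 95% confidence interval (for example Miettinen-Nurminen) in all randomized subjects.
- Keep Fisher's p-value as supportive.
- State that any claim of no increase in mortality rests on the upper confidence limit and not on p>0.05.

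The cost is a few sentences and one line of analysis code, with no new data or subjects. The downside is that the report will show openly that the excess is bounded only to within several percentage points.
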